### Intervention description {11a}

#### Investigational Medicinal Products (IMP) - bNAbs

The RIO trial involves administration of two bNAbs: 10-1074-LS and 3BNC117-LS, and placebo infusions (0.9% sodium chloride solution). 3BNC117-LS is a recombinant, fully human monoclonal antibody (mAb) of the IgG1κ isotype that specifically binds to the CD4 binding site (CD4bs) within HIV-1 envelope gp-120.

10-1074-LS is a recombinant, fully monoclonal antibody of the IgG1λ isotype that specifically binds to the base of the V3 loop within the HIV external membrane glycoprotein, gp120.

The original antibodies 3BNC117 and 10-1074 were identified and cloned at the Rockefeller University from an HIV-positive individual. Both 3BNC117-LS and 10-1074-LS differ from the original parental antibodies by two amino acid substitutions which were introduced for the purpose of extending their biological half-life.

Placebo arm B will receive 0.9% sodium chloride (normal saline) infusion identical in appearance and volume to the bNAb infusions.

Investigator brochures (IB) for 10-1074-LS and 3BNC117-LS IB will be used in the trial.

Both bNAbs will be stored at 5 ± 3 °C, and each bNAb vial contains a nominal 150 mg/ml of bNAb protein in a 1.0-mL buffered solution.

#### bNAb dosage and administration

3BNC117-LS and 10-1074-LS will each be administered at a dose of 30 mg/kg and 10 mg/kg respectively. Prior to infusion, each IMP is diluted to a final volume of 100 mL in a single normal saline injection. Each IMP is then administered as a separate intravenous infusion over a period of approximately 30 min per bNAb. IMP infusion should be administered through a 0.2 or 0.22 micron in-line filter.

#### Antiretroviral treatment interruption

Individuals on triple ART with suppressed HIV VL will be enrolled into the study and receive either dual bNAb or placebo, 3 days later they will then stop ART. The date of ART stop is considered time 0 for time to viral rebound estimation. At the time of recruitment, all participants will be receiving ART according to current best practice and the BHIVA guidelines [14]. At the time of randomisation, participants’ ART regimen must include an INSTI or bPI; if on an NNRTI, they must be switched to an INSTI or bPI at least 4 weeks prior to randomisation [16]. The ART regimen after viral rebound should ideally include an INSTI or bPI. Other changes in ART outside the protocol-mandated ART interruption period, and any other concomitant medical therapy either at screening or during the study will be recorded.

##### Management of ATI

Following interruption of ART, all participants will have their CD4 count and plasma HIV VL monitored using routine NHS validated measurements. These will be at a minimum weekly for the first 8 weeks and then every 2 weeks until viral rebound has occurred and/or ART is recommenced (according to any of the specified restart reasons) based on the thresholds described below. Results will be available within 24 h of laboratory receipt of samples. Results of the laboratory HIV VL will be given to the participant by the research study team, using the participant’s pre-stated preferred method (text, email, telephone, or in-person consultation).

Any study participant wishing to attend for additional visits for VL monitoring may do so. In exceptional circumstances (i.e. positive for SARS-Cov-2 or self-isolating), if participants are unable to attend in person for study visit, home visit will be arranged for the collection of blood sample for HIV VL monitoring.

##### Criteria for restarting ART

Viral rebound confirmed by HIV VL measurement from venous blood:
Sustained HIV viral load ≥1000 copies/ml for 6 weeks +/− 7 days.Is ≥100,000 copies/ml for two readings, 7 days apart +/− 7 days.Instances outside of the above two categories but are close to these definitions and necessitate ART restart for clinical reasons. These instances will be individually reviewed by an independent panel (Endpoint Adjudication Committee) to confirm if they meet the definition for viral rebound.CD4 count drops to less than 350 cells/μL.Clinical symptoms attributable to ATI.Participant preference.Major concerns over risk mitigation for HIV transmission.Positive for COVID-19 (SARS-CoV-2 PCR positive) during ATI.

The clinical decision algorithm for management of detectable viral load and viral rebound is summarised in Fig. 2. In addition,

**Fig. 2 Fig2:**
[figure not shown]
Monitoring protocol on analytical treatment interruption

At any VL threshold, if the participant prefers, ART can be restarted.It is possible that some participants will have consecutive VL that are repeatedly above and below 1000 copies/ml and therefore do not formally meet criteria for rebound, and yet have evidence of sustained viraemia. In these cases, the Endpoint Adjudication Committee will consider these instances and confirm whether they can be defined as viral rebound.If there is a confirmed drop in CD4 count to < 350 or in the presence of symptoms that maybe attributed to the ATI, ART will be recommenced.Restarting ART
Participants will be followed up at weeks 2, 4, 8, and 12 (with viral load testing) after reinitiation of ART or until their viral load becomes undetectable; they will be subsequently followed up until the end of the study. An additional venous blood sample (100 ml) will be taken at 16 weeks after restarting ART for research purposes.Any study participant who wishes to restart ART will be allowed to do so at any time during the ATI. Upon ART restart, the visit schedule will be as described above for participants restarting ART.

Participants who do not experience HIV rebound viraemia off ART within 36 weeks will continue to remain off therapy for the duration of the study or until viral rebound occur. At the end of the study, all participants will be recommended to restart ART irrespective of HIV viral load in accordance with BHIVA guidelines.

Participants will be clearly informed of the potential increased risk of onward transmission during the period off therapy, when there is a possibility of detectable viraemia. Participants will be advised to use condoms for all sexual contacts and be aware of the availability and access to post-exposure prophylaxis (PEP) for any HIV-negative partners should an exposure occur or if a condom breaks, particularly during ATI. In addition, any sexual partners of the participants wishing to discuss and access HIV pre-exposure prophylaxis (PrEP) will be invited to attend the RIO research team for HIV testing and where appropriate will be offered PrEP and be monitored through NHS sexual health clinics.

With the participant’s consent, their routine HIV clinician and general practitioner (GP) will be informed of their participation in the study.

### Criteria for discontinuing or modifying allocated interventions {11b}

#### bNAb dose modification for toxicity.

Rates of infusion of the bNab may be adjusted in the event of an adverse reaction. If this persists, the infusion will be halted.

### Strategies to improve adherence to interventions {11c}

#### Adherence to ART

ART treatment compliance will be the responsibility of each study participant and their routine HIV physician. Investigators will promote compliance by providing instruction for participants to take ART exactly as prescribed during the course of the trial. Participant compliance to ART or remaining off ART will be closely monitored throughout the trial through regular HIV viral load monitoring. Blood measurement of ART levels will be undertaken retrospectively to ensure that for evaluation of the primary endpoint individuals with controlled viraemia are not on any ART drugs.

#### Adherence to follow-up during ATI period

HIV viraemia will be monitored during ATI as described above.

If a participant does not attend a scheduled visit, the study clinical team must make reasonable attempts to contact the participant to remind them to attend as soon as possible.

If a further visit is missed, participants will be reminded of the risks to their own health and of onward viral transmission, and encouraged to restart ART. The use of condoms, PEP, and PrEP for HIV-negative partners to prevent onward transmission of HIV will be discussed and all HIV-negative partners will be linked into NHS PrEP services.

If a participant has missed study visits in a 4-week period, a letter will be sent to the participant, their routine HIV clinician and GP. A recommendation to restart ART would be given to these patients not attending follow-up visits during the ATI period, and they will continue to be invited to attend study follow-up visits until the end of the trial.

### Relevant concomitant care permitted or prohibited during the trial {11d}

#### Concomitant care prohibited during the trial.

Treatment with intravenous immunoglobulin or other monoclonal antibody treatments is prohibited for the duration of participation in the trial.

#### Concomitant care permitted during the trial.

Monitoring and medical care will be provided as per standard care, except during ATI where participants’ medical care will be provided as described above.

### COVID-19 pandemic measures

All study visits will take place in COVID-19 free areas and participants will be provided appropriate personal protective equipment (PPE), and trial procedures conducted as per current COVID-19 guidelines/practices [17] until such guidelines/practices are no longer applicable or relevant.

A protocol amendment was introduced to the eligibility criteria that participants would only be included if they had received at least one dose of a SARS-CoV-2 vaccine. Single-dose vaccine efficacy of the BNT1626b2 mRNA vaccine (Pfizer BioNTech) and ChAdOx1 nCoV-19 vaccine (AZD1222) has been estimated to be high at 89% and 73% respectively [18], and contributed to the rationale to offer enrollment to participants while awaiting their second dose in the vaccine schedule recommended by the UK joint committee on vaccination and immunisation [19]. In a HIV-positive cohort, there were no differences in both humoral and cell-mediated immune responses produced by the ChAdOx1 nCoV-19 vaccine compared to a HIV-negative cohort [20].

If participants exhibit SARS-CoV-2 symptoms during ATI or any other time during the trial, participants will be tested for SARS-CoV-2. If PCR positive for SARS-CoV-2, individuals who have interrupted ART will be asked to restart ART. A review with the CI, PI, participant, and their clinical team, on a case-by-case basis, will evaluate whether repeat ATI will be undertaken, after clearance of SARS-CoV-2 and resolution of symptoms. All study participants will have access to current/ongoing recommended NHS COVID-19 treatment.

### Provisions for post-trial care {30}

At the end of the study, all participants will be recommended to restart ART irrespective of HIV VL in accordance with BHIVA guidelines.

Participants will be referred to their routine HIV clinic for ongoing care and follow-up post-trial.

Admission to hospital if required will be provided to all study participants through NHS clinical services.

### Outcomes {12}

The primary endpoint is the comparison of time to viral rebound within 36 weeks after initial ATI, during Stage 1, summarised by hazard ratios.

Secondary endpoints, for both stages 1 and 2, are:
Safety defined as the number and types of adverse events (AEs) and serious adverse events (SAEs) by groupLength of time undetectable in days following ATI in the absence of detectable ART (comparing arm A vs B and arm B Stage 1 ATI vs Stage 2 ATI), summarised by mean.CD4 T cell counts and CD4:CD8 ratios at weeks 12-, 24-, 36-, and 48-week post randomisation, and 12-weekly until the end of study participation by arm, summarised by median.Percentage of participants with undetectable VL at week 12, 24, 36, and 48 post randomisation (Stage 1; arm A vs B) and then for arm B participants post second ATIQuantitation of proviral HIV DNA and cell-associated RNA at baseline and following viral rebound and resuppression on ART by arm.Duration of remission analysed under multiple alternate definitions (e.g. VL < 40 copies/mL, < 400 copies/mL, < 1000 mL), comparing arm A vs B and arm B Stage 1 ATI vs Stage 2 ATI, summarised by mean.Time to restarting ART after start of ATI, comparing arm A vs B and arm B Stage 1 ATI vs Stage 2 ATI, summarised by median.Time to undetectable HIV VL after restarting ART, comparing arm A vs B and arm B Stage 1 ATI vs Stage 2 ATI, summarised by median.The proportion of participants with detectable ART levels in blood during ATI, at weeks 12, 24, 36, and 48 post randomisation, by arm.bNAb concentration in blood at dosing, weeks 2, 4, 8, 12, 24, 36, and 48, time of viral rebound, and end of study, summarised by mean.Proportion and description of bNAb resistance/sensitivity at pre and post infusion time-points, by arm.Descriptive changes in reported HIV Quality of Life measures at baseline, 2 weeks after infusion, and at the end of study [21].

Tertiary or exploratory endpoints, for both stages 1 and 2, will include:
HIV-specific (humoral and cell-mediated) and innate immune responsesImmune phenotyping and activation/exhaustionHost gene expressionViral sequence and integration site analysisMeasures of the HIV viral reservoir in CD4+ T cells.

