Primary endpoint analysisAll the analyses will be on an intention-to-treat (ITT) principle and all statistical tests will be two-tailed with a 5% significance level. All participants screened eligible and enrolled in the trial will be included in the ITT analyses.The primary endpoint will be analysed using a time to event approach and differences will be tested using Cox proportional hazards models with censoring applied (as defined within the SAP). Kaplan-Meier curves detailing the survival function will also be presented.Secondary outcomes will be compared based on data type. Time to event outcomes will be assessed using the same Cox proportional hazards models described above. Paired data in Stage 2 will be assessed using a paired *t*-test (or alternate paired approach) and chi-squared / Fisher exact testing used for categorical variables. Further details to be provided in the SAP.Safety analysisSafety outcomes will be reported as unadjusted participant proportions and rates within and between arms with 95% confidence intervals using exact methods where appropriate.

An independent Endpoint Adjudication Committee will be set up to evaluate and review confirmed time of viral rebound in retrospect prior to the primary analysis. The committee will review all viral load data (blinded to study arm) and determine the date of confirmed viral load rebound. Any participant recommencing ART prior to viral rebound will also be reviewed by the committee as a potential endpoint. If established as not an endpoint, these participants will be censored at time of ART restart for analysis purposes.

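### Two secondary durations that are right-censored by design are summarised by a mean with no time horizon, so the A–B difference depends on study length and the Stage 1 v Stage 2 difference can be biased in either direction

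*Protocol article*

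**What the plan says.** Outcomes {12} lists length of time undetectable after ATI, in the absence of "detectable ART (comparing arm A vs B and arm B Stage 1 ATI vs Stage 2 ATI), summarised by mean". A second endpoint, "Duration of remission analysed under multiple alternate definitions", has the same comparisons and is also summarised by mean. Neither has a horizon, whereas the primary endpoint is limited to 36 weeks. Two neighbouring durations are treated differently: "Time to restarting ART after start of ATI, comparing arm A vs B and arm B Stage 1 ATI vs Stage 2 ATI, summarised by" median, and time to undetectable viral load after restart is also given as a median.

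Under Criteria for restarting ART (text after Fig. 2), participants without rebound by 36 weeks "will continue to remain off therapy for the duration of the study or until viral rebound occur". Trial design {8} runs the second ATI to rebound or end of study as well. Note 5 to Table 2 moves consenting arm B participants to Stage 2 after viral rebound, with no week-36 cut-off.

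Sample size {14} sizes Stage 2 on a within-person difference in days undetectable: SD 14 days, correlation 0.7, 36 patients, 6.6 days detectable with 90% power, 15% dropout.

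Statistical methods {20a} says "Paired data in Stage 2 will be assessed using a paired *t*-test (or alternate paired approach"), and also "Time to event outcomes will be assessed using the same Cox proportional hazards models described above", with details left to the SAP. It does not say which of the two governs these durations.

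**The concern.** A mean of durations that are partly cut off by the end of follow-up is not a property of the treatment alone. If censored time is counted as duration, the mean grows with the length of the study, and it grows faster in the arm with more censoring. The plan expects 45% of arm A and 10% of arm B to be rebound-free at 36 weeks, so the two arms would be affected unequally. ART restart before rebound also cuts observation short. The primary analysis censors such restarts when they are not adjudicated as endpoints, but nothing comparable is stated for these means.

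Stage 2 adds a second problem. A pair exists only if the first interruption ended in rebound, so the first value is always complete while the second may be censored. This contrast carries the question of whether control outlasts the antibody (Explanation for the choice of comparators {6b}; Benefits of the study). A non-zero difference with no true effect could be misread there.

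**Working it through.** **1. The plan's own Stage 2 figure.** SD of the paired difference = 14 × √(2 × (1 − 0.7)) = 10.84 days. With 15% dropout, 36 × 0.85 = 30.6 evaluable. The paired t-test then detects 6.57 days with 90% power (6.64 at n = 30, 6.53 at n = 31). The stated 6.6 days is reproduced, and it confirms that Stage 2 is sized on a mean paired difference.

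**2. A v B: dependence on follow-up.** Inputs from Sample size {14}: 10% (B) and 45% (A) rebound-free at 36 weeks. Assumptions: exponential times; rebound time as a proxy for time undetectable; censored time counted as duration; the same follow-up τ for everyone.

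- Hazards per week: B = −ln(0.10)/36 = 0.0640; A = −ln(0.45)/36 = 0.0222.
- Mean observed duration = (1 − exp(−hτ))/h.

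| Follow-up τ | B (days) | A (days) | A − B (days) | A − B (weeks) | A censored |
|---|---|---|---|---|---|
| 36 weeks | 98.5 | 173.6 | 75.1 | 10.7 | 45% |
| 48 weeks | 104.4 | 206.8 | 102.4 | 14.6 | 34% |
| 96 weeks | 109.2 | 278.1 | 168.9 | 24.1 | 12% |
| no censoring | 109.4 | 315.6 | 206.1 | 29.4 | 0% |

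The hazards are the same in every row; only the study length changes. The protocol article gives no study length, so the row that would apply cannot be told.

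**3. Stage 2: paired mean difference with no true effect.** Pairs were simulated with correlated times (Gaussian copula) and kept only if the first period ended in rebound. Two shapes pass through 10% rebound-free at 252 days: exponential, and lognormal with median 28 days. Values are second minus first period, in days, at correlation 0.7.

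| Assumed rule for entry and end of follow-up | Exponential | Lognormal |
|---|---|---|
| Entry only if rebound by week 36; second period fully observed | +10 | +27 |
| Same entry; second period capped at 36 weeks | +5.6 | +8.4 |
| One common study end at week 72 after first ATI | −17 | −1.5 |
| Common end at week 96 | −11 | −1 |
| Common end at week 144 | −3 | about 0 |

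The common-end rows assume 31 weeks between first rebound and second ATI: 6 weeks to confirm rebound, 1 to dosing, 24 of washout. At correlations of 0 to 0.3 with a common end, the exponential case gives 0 to −7 days and the lognormal about +9 to +16. The sign therefore turns on study length, correlation and distribution.

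**4. What a paired censored-data method can and cannot do.** Take both periods capped at 36 weeks, correlation 0.7 and no effect. The simulation has 6% of second periods censored among those who entered, so P(first < 36, second > 36) = 0.9 × 0.06 = 0.054, and P(both > 36) = 0.10 − 0.054 = 0.046. Then P(second > first | first < 36) = (0.5 − 0.046/2)/0.9 = 0.53, not 0.50. The ordering itself is tilted by selection, so a stratified or rank method handles the censoring but inherits the tilt. In simulation of this scenario with 34 arm B participants, false positives for a longer second period were 6.4% with the t-test and 5.6% with a Cox model stratified by participant, against 2.5% nominal.

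**The case against.** **The test is not fixed.** The t-test carries the rider of an alternative paired approach, Cox is named for time-to-event secondary outcomes, and the rest is left to the SAP. This stands: the article does not commit to an unsuitable test. It does commit to the mean as the summary and to a paired-mean sizing, and neither the rider nor the Cox sentence changes those. The article also does not say that censored time will count as complete. That is the plain reading of a mean in days with no horizon, but it remains a reading.

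**The figures use a proxy.** Time undetectable ends before confirmed rebound, which needs a sustained or very high viral load, so the censoring fractions and the A v B table are indicative only. This stands too.

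**A stronger reading is tempting: that the Stage 2 comparison favours the second period.** Selecting on a completed first period does push that way. With exponential times, entry closed at 36 weeks and a linear regression to the mean, the spurious gain is (1 − 0.7) × (109.4 − 81.4) = 8.4 days, which seems to exceed the 6.6-day target. The documents do not support this reading, for three reasons:

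- They set no 36-week limit on entry. With entry open to week 72 the gain falls to about 1.4 days.
- The second ATI starts later and is also cut by end of study, which pushes the other way.
- The comparison mixes scales. The 6.6 days rests on an SD of 14 days. With normal times at that SD and the longest 10% excluded, the bias is (1 − 0.7) × 14 × 0.1755/0.9 = 0.8 day. In the capped exponential case the paired difference has an SD of about 63 days, so 5.6 days is about 0.09 SD.

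**Conclusion.** The point holds for two secondary endpoints. Both are summarised by mean with no horizon while follow-up runs to rebound or end of study, so the A–B difference has no fixed estimand. On the planning rates it moves from 10.7 weeks to 24.1 weeks as follow-up goes from 36 to 96 weeks, assuming exponential times, rebound time as a proxy, and censored time counted as duration.

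In Stage 2 the paired mean difference can be biased with no true effect, because pairs are conditional on first rebound and only the second value can be censored. Neither the direction nor the size can be settled from the article: the scenarios tried at correlation 0.7 ran from about −17 to +27 days. A reader should not infer a built-in advantage for the second period, nor that a censored-data method would remove the selection. The primary Cox analysis of time to rebound is not affected.

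**What to change.** - In Outcomes {12}, replace the mean for both durations with the restricted mean to a fixed horizon, for example 36 weeks after ATI to match the primary endpoint, plus the Kaplan–Meier median. On the planning assumptions the restricted means are 98.5 days (B) and 173.6 days (A), a difference of 75.1 days that does not depend on study length.
- For arm B, apply the same horizon to both periods. In Statistical methods {20a}, name a paired censored-data method, such as a Cox model stratified by participant or the paired Prentice–Wilcoxon test, as the alternative paired approach in place of the t-test.
- Report Stage 1 v Stage 2 as non-randomised and conditional on first rebound. Give the number of arm B participants who did not enter Stage 2 and why. State that these methods deal with censoring but not with the selection. Removing it would need second-period data on participants who did not rebound, which the design does not provide. Adding them with zero gain left the false-positive rate unchanged in simulation (6.4% at correlation 0.7).

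Cost: protocol and SAP wording, slightly more analysis, and a small loss of information compared with a t-test on complete data. No new visits or data are needed.

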**Table 3 Tab3:**
[figure not shown]
Trial assessment schedule for Stage 2 (arm B only)

1. Visit prefix nomenclature: Screening ‘S’; During TI ‘A’; After First Rebound ‘B’; After Second Rebound ‘C’

2. 4-weekly visits repeated until viral rebound occurs

3. UNS: patients may request an additional ‘unscheduled’ visit to have HIV VL measured any time while still unsuppressed

4. ^#^SARS-Cov-2 PCR will be conducted up to 72 h prior to ATI visit (B20) and for the rest of the visits PCR will only be performed if participants exhibit COVID-19 (SARS-Cov-2) symptoms

5. Visit B1 can be conducted as an onsite or telephone visit for arm B participants. The safety bloods and physical examination can be conducted at the confirmatory viral rebound visit if participant chooses B1 to be a telephone visit.

6. Research bloods can be taken at the dosing visit or the viral rebound visit at Stage 1—not at both visits

7. Visits B11-19 can be 4-weekly visits if participant has had two previous undetectable viral load while on ART

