#### Blood tests after screening:

The following blood tests will be repeated as indicated; tests will be analysed via local laboratories:
LFTs (*weeks 1, 2, 4, 8, fortnightly till viral rebound*)Biochemistry: (*Stage 1: screening visit, dosing visit, week1, viral rebound visit and 12 weeks post-viral rebound. Stage 2 visits include: week 1, week 2, and 12 weeks after viral rebound*)*Full blood count (FBC) as per visit schedule*, CD4 count, CD8 count, CD4:CD8 ratio, and HIV VL (*all visits*)

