#### Peripheral blood mononuclear cells (PBMC) and plasma samples

Blood samples (between 50 and 200 ml depending on the time-point) for the collection of PBMCs and plasma will be taken to evaluate the parameters detailed in Table 4.

For arm A, samples will be collected according to the schedules in Table 2 at the following time-points: screening, dosing visit, week 8, 24, and 36 after ATI, at viral rebound on restarting ART, following resuppression 16 weeks after ART restart. For participants who maintain undetectable VL off ART after 36 weeks, a 50-ml blood sample will be taken fortnightly until rebound or the end of the study.

For arm B, samples will be collected according to the schedules in Table 3 at the following time-points: screening, dosing visit, weeks 8, 24, and 36 after ATI, at viral rebound on restarting ART. For participants who maintain undetectable VL off ART after 36 weeks, a 50-ml blood sample will be taken fortnightly until rebound or the end of the study.

Then, bloods will be taken again at bNAb dosing (1 week after ART restart), at start of 2nd ATI 24 weeks later, 8 weeks after start of 2nd ATI, and then fortnightly from 24 weeks after the 2nd ATI until rebound or the end of the study. Following rebound and ART restart, bloods will be taken at restart and following resuppression 16 weeks after ART restart.

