### Potential risks of the study

#### Risk of the intervention (bNAbs)

The use of bNAb infusions is experimental with, at time of writing, an estimated 27 (including 6 HIV-positive individuals) and 43 (including 15 HIV-positive individuals) study participants having received 10-1074-LS and 3BNV117-LS respectively. In total, 40 participants (including 5 HIV-positive individuals) have received both antibodies simultaneously in studies that had stopped recruitment or completed [28]. Studies with either bNAbs are ongoing (Table 1) and more data will be available on an ongoing basis.

As with all antibody infusions, there is a risk of anaphylaxis to the protein, and close monitoring will be necessary within a Clinical Research Facility. This requires well-trained clinical staff, access to intensive medical support if necessary, and monitored review of the participant both before, during, and at least an hour after completion of the infusion. To date, there have been no reported cases of anaphylaxis to either of the bNAbs included in the study [[name] personal communication]. Mild local and systemic reactions may be observed, and participants will have a weekly medical review including regular health screening questions, for the first 8 weeks after receipt of the infusions, and subsequently twice monthly. Infusion of antibodies carries a potential risk of thromboembolism, and coagulation screening tests will be performed at screening. Individuals at increased risk of thromboembolic disease will not be eligible for inclusion in the study.

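### Time to undetectable viral load after ART restart appears to be read on a sparse visit grid for some restarts and a denser one for the arm B restart that opens Stage 2, which can by itself create a difference in both planned comparisons

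*Protocol article*

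**What the plan says.** All places are in the Protocol article.

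- **Endpoint.** Outcomes {12}: "Time to undetectable HIV VL after restarting ART, comparing arm A vs B and arm B Stage 1 ATI vs Stage 2 ATI, summarised by" the median. Two comparisons are fixed: arm A with arm B, and arm B after its first interruption with arm B after its second.
- **General rule after restart.** Under Criteria for restarting ART (text with Fig. 2): "Participants will be followed up at weeks 2, 4, 8, and 12 (with viral load testing) after reinitiation of ART", or until VL is undetectable. No arm or stage is excepted.
- **Arm B moves to another schedule.** Table 2, note 5: arm B participants who agree go to Stage 2 after rebound and B1 follows the Stage 2 schedule; those who decline stay on the Stage 1 schedule. Trial design {8} has Stage 2 begin with that same restart.
- **Stage 2 visits.** The Table 3 notes make B20 the second-interruption visit and add: "Visits B11-19 can be 4-weekly visits if participant has had two previous undetectable viral load while on ART".
- **Timing of the dose.** Peripheral blood mononuclear cells (PBMC) and plasma samples: "bloods will be taken again at bNAb dosing (1 week after ART restart), at start of 2nd ATI 24 weeks later". Trial design {8} describes the infusion as immediate.
- **Review after infusion.** Risk of the intervention (bNAbs): "participants will have a weekly medical review including regular health screening questions, for the first 8 weeks after receipt of the infusions", then twice monthly.
- **When VL is taken.** Blood tests after screening lists "CD4 count, CD8 count, CD4:CD8 ratio, and HIV VL" for all visits.
- **Analysis.** Statistical methods {20a}: Cox models for secondary time-to-event outcomes, and a paired t-test or other paired method for Stage 2 pairs.

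**The concern.** The recorded value of this endpoint is the date of the first undetectable reading, so it depends on when VL is read. A participant who truly suppresses at 4.5 weeks is recorded at week 8 on a 2/4/8/12 grid and at week 5 on a weekly grid.

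The restart that ends arm B's first interruption enters both comparisons, and it is the one that appears to sit on the denser grid. Arm A's restart, and arm B's restart after the second interruption, fall under the 2/4/8/12 rule. With identical true times, arm B would tend to look faster than arm A, and arm B's second restart slower than its first. The first could be credited to bNAbs given around restart, and the second blamed on the second interruption. This is separate from the confounding by the bNAbs themselves: the artefact arises even if they have no effect on resuppression.

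**Working it through.** **1. No plan figure to reproduce.** The protocol gives no expected resuppression time and no power for this endpoint. From Sample size {14} only the rebound rates are used, to size an illustration: 0.55 × 36 = 19.8, about 20 restarts in arm A; 0.90 × 36 = 32.4, about 32 in arm B.

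**2. How dense is the Stage 2 grid?** B1 to B20 is 19 gaps. The second interruption comes 24 weeks after dosing, and dosing is at restart or 1 week later, so the span is 24 to 25 weeks.

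- Mean gap: 24/19 = 1.26 to 25/19 = 1.32 weeks.
- If B11 to B20 are fortnightly (assumed; 9 gaps, 18 weeks), the 10 gaps from B1 to B11 average (24 − 18)/10 = 0.6 to (25 − 18)/10 = 0.7 week.
- Four-weekly spacing for B11-19 is a relaxation allowed only after two undetectable results, so the default there is denser.

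Together with weekly review after infusion and VL at all visits, this points to a grid clearly finer than 2/4/8/12. It does not establish exactly weekly.

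**3. Effect of the grid alone.** Assumptions: log-normal true times, the same for both restarts; recorded time is the first scheduled reading at or after the true time. Sparse grid: weeks 2, 4, 8, 12, plus 16 as a last reading. Dense grid: weeks 1-9, then fortnightly. Log-SD 0.4 or 0.6.

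| True median (wk) | Recorded median, sparse | Recorded median, dense | Mean shift (wk) |
|---|---|---|---|
| 1.5 | 2 | 2 | 0.4-0.6 |
| 2.5 | 4 | 3 | 0.7-0.8 |
| 3.5 | 4 | 4 | 1.0-1.1 |
| 5 | 8 | 5.5-6 | 1.2-1.4 |
| 6 | 8 | 6-7 | 1.2-1.4 |
| 7.5 | 8 | 8 | 1.1-1.3 |
| 9 | 12 | 9-11 | 1.0-1.2 |

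The mean is later on the sparse grid in every row. The median moves in some rows only.

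**4. False-positive rate, log-rank, nominal two-sided 5%, no true effect.** With 20 against 32 participants, log-SD 0.5 and true medians from 2 to 7.5 weeks:

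- Stage 2 grid weekly for 8 weeks, then fortnightly: about 18-49%.
- Stage 2 grid fortnightly throughout: about 6-25%.
- Same 2/4/8/12 grid in both arms: about 4-7%.

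Over the wider scenarios of step 3, with 36 against 36, the log-rank rate was 15-87%. A paired t-test with 31 pairs (36 less 15%, correlation 0.7 between log times) gave 36-92%.

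**The case against.** **The weekly grid is not written down.** A reader might infer that the protocol prescribes weekly VL after arm B enters Stage 2. It does not. The Table 3 grid is not shown, the sentence on weekly review is a safety statement in the Discussion that does not mention VL, and B1 may be a telephone visit. The one explicit rule on VL after restart, read literally, gives every restart the same grid and hence no artefact. This stands, and it is why the point is conditional. But that reading is hard to square with Table 2 note 5 and the B1-B20 numbering.

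**The planned summary is the median.** A reader might infer that the dense grid always looks faster. That is safe for means and hazards, not for medians, which agree when the true median is about 1.5, 3.5 or 7.5 weeks. It limits the damage to the descriptive summary but does not protect the Cox or paired analyses.

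**The inputs are assumed and the contrast is diluted.** True suppression times are not in the document. Arm B participants who decline Stage 2 keep the Stage 1 schedule, and anyone still unsuppressed may request extra VL readings. Both narrow the gap, so the rates in step 4 lean high.

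**Derivation rules belong in the SAP.** True in general, and the SAP may already deal with this. However, the protocol itself fixes the endpoint, both comparisons, the restart grid and the class of model, and together these can set unequal grids against each other.

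**Neither contrast is a clean test of bNAbs anyway.** Also true, but that is a different problem and does not remove this one.

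**Conclusion.** The concern holds conditionally. If the restart that opens Stage 2 is read on a denser grid than weeks 2, 4, 8 and 12, as the visit numbering suggests, unequal reading times bias both planned comparisons with no true difference. The mean shift is about 0.4 to 1.4 weeks against a near-weekly grid. The recorded median shifts by zero to about 3 weeks, depending on where the true median falls. Log-rank false-positive rates are illustratively 18-49% (weekly) or 6-25% (fortnightly), lower once decliners and unscheduled readings are allowed for.

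This rests on an inferred Stage 2 grid and on assumed log-normal suppression times. It concerns one secondary endpoint. A reader should not carry it over to time to viral rebound or to the Stage 1 sample size, neither of which uses readings after restart. It should be corrected, because the derivation is cheap to settle in advance.

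**What to change.** 1. Reconcile the general restart rule with the Stage 2 schedule, and state which VL readings follow the restart that opens Stage 2. The two descriptions of when the infusion falls relative to that restart (immediate, or 1 week after) must also be reconciled, since they decide how Stage 2 visits map to weeks since restart.
2. Derive the endpoint for every arm and period only from readings at weeks 2, 4, 8 and 12 after ART restart, ignoring extra Stage 2 and unscheduled VLs, and report the median from that derivation. Set a visit window: if Stage 2 visits are counted from a dose given at week 1, weekly review ends at week 1 + 8 = 9 and fortnightly visits then fall at weeks 11 and 13, so week 12 has no exact visit.
3. Alternatively, analyse the time as interval-censored between the last detectable and the first undetectable reading, which uses all readings.

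The cost is wording in the endpoint definition and the SAP. No visit, sample or treatment changes. Under option 2 the finer arm B timing is left out of the comparison, though it can still be described.
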